# The UPDATE trial (*UVB*
*P*hototherapy in *D*ermatology for *AT*opic *E*czema): study protocol for a randomized controlled trial of narrowband UVB with optimal topical therapy versus optimal topical therapy in patients with atopic eczema

**DOI:** 10.1186/s13063-024-08334-z

**Published:** 2024-07-16

**Keywords:** Atopic eczema, Atopic dermatitis, Phototherapy, NB-UVB, Topical therapy, Optimal topical therapy, Effectiveness, Cost-effectiveness, Safety, Randomized controlled trial

## Abstract

**Background:**

Narrowband ultraviolet B (NB-UVB) phototherapy is commonly prescribed for patients with moderate-to-severe atopic eczema (AE). The efficacy of NB-UVB, however, has not yet properly been established, as current evidence is of low certainty. Our aim is to assess the short-term and long-term (cost-)effectiveness and safety of NB-UVB in adult AE patients by performing a pragmatic, multicenter, prospective, randomized, open-label, blinded-endpoint (PROBE) trial. This protocol outlines its methodology.

**Methods:**

A pragmatic, multicenter, PROBE trial will be performed with 1:1 randomization of 316 adult patients with moderate-to-severe AE who have inadequate disease control with topical therapy and who are eligible for optimal topical therapy (OTT) or NB-UVB in combination with OTT as a next step. Participants in the interventional arm will receive a minimum of 3 months of OTT combined with 8 to 16 weeks of NB-UVB. The control group receives 3 months of OTT. Following the interventional phase, follow-up will continue for 9 months. Physician-reported and patient-reported outcomes (according to the Harmonising Outcome Measures for Eczema (HOME) Core Outcome Set) and adverse events are assessed at 4 weeks, 3, 6, 9, and 12 months.

**Discussion:**

The UPDATE trial aims to provide high-quality evidence regarding the (cost-)effectiveness and safety of NB-UVB phototherapy in moderate-to-severe AE patients. Challenges that are addressed in the protocol include the possible bias arising from applying open-label treatment and the necessity of introducing OTT into the study design to prevent a high dropout rate.

**Trial registration:**

ClinicalTrials.gov NCT05704205. Registered on December 8, 2022.

**Supplementary Information:**

The online version contains supplementary material available at 10.1186/s13063-024-08334-z.

## Introduction

### Background and rationale

Atopic eczema (AE) (syn. atopic dermatitis) is a dermatological condition characterized by a chronic fluctuating pruritic inflammation of the skin. It is a common disease that affects 2–10% of the adult population, thereby posing a high burden in terms of health care costs [1–3]. According to the World Health Organization (WHO) Global Burden of Disease project, AE is in the top 50 of the most prevalent diseases worldwide and is the leading skin condition regarding disease burden measured by disability-adjusted life years (DALYs) [4].

In clinical practice, AE can be treated using a stepped-care approach [5, 6]. Patients whose AE is insufficiently controlled by standard topical care are eligible for optimal topical therapy (OTT), phototherapy, or systemic immunomodulating therapy.

OTT entails a combination of a personalized topical regimen with detailed instructions (including the fingertip unit method) and lifestyle recommendations, including advice regarding washing/bathing, avoidance of triggers and contact allergens, and psychological support. In the 2022 European guideline (EuroGuiDerm) on AE recommendations and suggestions for the optimal topical care of AE patients based on expert consensus can be found [5, 6].

Phototherapy is a frequently initiated first-line therapy for moderate-to-severe AE; it is prescribed by approximately 85% of European dermatologists as highlighted by a survey performed in 2018. Types of phototherapy include, i.e., photochemotherapy (PUVA), ultraviolet A-1 (UVA1), broadband ultraviolet B (BB-UVB), and narrowband ultraviolet B phototherapy (NB-UVB). The 2018 survey clarified that NB-UVB is the most commonly applied type (80.9%) [7]. NB-UVB devices contain fluorescent lamps emitting UVB in the 311 nm to 313 nm range. Guidelines on the dosimetry of NB‐UVB have mainly been published for psoriasis [8–12], but these dosing protocols are often also used for AE, as dosing studies for AE are not available.

High-quality evidence for the efficacy, (cost-)effectiveness, and safety of NB-UVB, however, does not exist for AE. Remarkably, NB-UVB for AE has only been studied in few short-term (9–12 weeks) and low-to-moderate-quality randomized controlled trials (RCTs) [13]. Recently, a Cochrane systematic review assessed the currently available evidence on the different phototherapy options for AE [14]. It concluded that NB-UVB is safe and effective in AE patients and may improve physician-assessed AE signs and patient‐reported symptoms when compared to placebo. However, firm conclusions could not be drawn due to the available evidence being of very low to low certainty. It therefore remains unclear whether NB-UVB is (cost-)effective for the treatment of AE.

Recently, this lack of evidence has resulted in the imminent discontinuation of reimbursement of phototherapy for AE in the Netherlands by some health insurance companies [15]. Discontinuation of reimbursement of NB-UVB will lead to the loss of this therapeutic option. This may lead to a shift to new on-label and much more expensive systemic treatments (each with its own safety profile) that have been proven effective in RCTs. Besides, patients and dermatologists often hesitate to initiate systemic therapy (reasons include but are not limited to the costs of these treatments and the possibility of side effects) and hope to postpone this next step with phototherapy. In some patients, such as patients with a child wish, many topical and systemic therapies are not suitable. It is therefore important that this type of phototherapy is further investigated in a well-designed RCT to establish if NB-UVB should still have a place in the treatment algorithm.

### Objectives

The aim of the UPDATE trial is to investigate the short-term and long-term effectiveness, cost-effectiveness, and safety of NB-UVB + OTT versus OTT alone in the treatment of adult patients with moderate-to-severe AE who have inadequate disease control with topical therapy and who are eligible for OTT or NB-UVB + OTT as a next step. This will be investigated in a pragmatic, multicenter, prospective, randomized, open-label, blinded-endpoint (PROBE) trial with 1:1 allocation in a superiority framework [16].

## Methods and trial design

### Study setting

This study will be conducted in Dutch secondary and tertiary care centers. The listing of participating clinics and hospitals can be found on www.ClinicalTrials.gov, identifier NCT05704205.

### Eligibility criteria

Adult patients with moderate-to-severe AE who have inadequate disease control with their current topical treatment will be included in this study. A variety of topical treatments may have been tried including topical corticosteroids, calcineurin inhibitors, coal tar preparations, and emollients with more or less specific instructions due to the limited time in most secondary care settings. They are eligible for OTT or NB-UVB + OTT as a next step.

### Inclusion criteria

In order to be eligible to participate in this study, a subject must meet all of the following criteria:Adult (≥ 18 years of age) patient meeting the UK working party criteria for AE [17];AE insufficiently controlled by standard topical care and therefore eligible for OTT or NB-UVB;Validated Investigator Global Assessment for Atopic Dermatitis (vIGA-AD) of ≥ 2 (moderate disease);Eczema Area and Severity Index (EASI) of ≥ 7 (moderate disease); andAbility to provide written informed consent.

### Exclusion criteria

A potential subject who meets any of the following criteria will be excluded from participation in this study:Contra-indication for NB-UVB [18];Genetic defects associated with photosensitivity or skin cancer;Heavily photo-damaged skin;History of melanoma or non-melanoma skin malignancies (in case of basal cell carcinoma patient is excluded if one has a history of > 2 basal cell carcinomas);Use of systemic immunosuppressants/immunomodulators;Use of medication associated with photosensitivity;Patient is already on systemic AE therapy;Patient is already on OTT for the past 2 months; andNB-UVB or any systemic therapy with influence on AD in the past 9 months.

A course of prednisolone of 15 days or more is regarded as systemic AE therapy.

### Informed consent

Subjects will be recruited from the patient population of each participating center. Possible eligible patients will be informed verbally about the study by a trained investigator. This may be in person or via telephone/video call. The patient will receive the participant information sheet and informed consent form (ICF) digitally or in print. Patients who agree to participate will be asked for written informed consent after reviewing the abovementioned information during a reflection period of at least one hour. In order to schedule the screening activities, it is allowed that the patient gives oral consent. The oral consent must be documented in the digital patient file. At the appointment of the screening activities the patient and the investigator will sign the informed consent form together. Allocated therapy cannot start before both parties have signed the ICF.

On the consent form, participants will be asked if they agree to the usage of their data should they choose to withdraw from the trial. Participants will also be asked for permission for the research team to share data to investigators, auditors, or regulatory authorities, where relevant. No ancillary studies are planned. This trial does not involve collecting biological specimens for storage.

### Interventions

We will investigate a course of NB-UVB + OTT (home or out-patient) of 12 weeks (range of at least 8 weeks and up to 16 weeks) compared to OTT alone. In the interventional arm, NB-UVB will be given 3 times per week with daily OTT. In the control group daily OTT will be applied.

#### Intervention description

##### NB-UVB

Both outpatient clinic and at-home NB-UVB will be assessed. The ultraviolet emission from phototherapy booths and panels is made possible by UVB lamps. NB‐UVB devices contain fluorescent lamps emitting UVB in the 311 nm to 313 nm range [19].

In the out-patient clinic administration of NB-UVB rays will be executed according to the manufacturer’s instructions by trained nurses. Patients undergoing at-home therapy will receive detailed instructions on the treatment procedure prior to starting NB-UVB. During the course participants will be remotely monitored via the site’s affiliated phototherapy panel supplier, following the local procedure. During administration, all patients will wear protective goggles and cover the genital area to shield the eyes and scrotum/vulva from ultraviolet rays. Administration will occur three times a week.

The patient’s initial dosing and dosage modification during phototherapy will be done according to a standardized study dose regimen (Additional file 2). During NB-UVB treatment, the researcher (or if the researcher is not a physician: the researcher together with a supervising physician) will monitor therapy response and tolerability and determine treatment duration (minimum of 8 weeks, maximum of 16 weeks).

After completing the NB-UVB course and applying 3 months of OTT (as listed below), patients are allowed to take the next step in the AE treatment algorithm if needed, being one of the currently available systemic immunomodulating therapies.

##### OTT

All participants will use daily OTT. This consists of detailed instructions about the disease, corticophobia and treatments by trained nurses, bathing and showering advices, adequate emollients use, avoidance of triggers (including possible and proven contact allergens), fingertip unit (FTU) explanation and a personalized scheme of topical therapy with topical corticosteroids (TCS) of different potencies, topical calcineurin inhibitors (TCI), and tar ointments, based on the recommendations on the use of topical therapy in national and international guidelines [6, 18, 20].

In the NB-UVB + OTT group, patients are allowed to apply topical therapies two hours after UV irradiation. Patients will use OTT for at least 3 months guided by standardized informational material. All patients will be instructed to keep empty tubes of their used topical treatment (excluding emollients) and to bring them to the appointments in order to analyze potency and quantities between the NB-UVB + OTT vs OTT group.

After 3 months of OTT, if needed, patients are allowed to take the next step in the AE treatment algorithm, being one of the currently available systemic immunomodulating therapies. During follow-up, patients from the OTT group are not allowed a NB-UVB course.

##### Rescue medication

For patients in the NB-UVB + OTT group, if sunburn occurs during NB-UVB, rescue medication consists of a one-time topical application of a class IV corticosteroid. For all patients, in case of severe uncontrolled AE during the study that requires rescue medication, a short course of oral prednisone can be prescribed [21]. Dosage and duration of this course will be determined by the treating physician. At the investigators’ discretion, rescue medication is allowed in other situations after consulting with the coordinating investigator.

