##### Secondary outcome

Physician-reported clinical signs at 1–3–6–9–12 months:Delta EASIPercentage of patients with EASI50vIGA-AD (range 0–4) [25].Time until a 25% reduction in mean EASI is achievedType, frequency, and quantity of topical therapies usedTime to switch to systemic therapyUse, amount, and duration of rescue medicationPatient-reported symptoms at 1–3–6–9–12 months:PGA (Patient Global Assessment) (range 0–4) [26].POEM (Patient-Oriented Eczema Measure) (range 0–28) [27, 28].NRS-11 (Numeric Rating Scale) for peak itch over the past 24 h (range 0–10) [29].Patient-reported quality of life at 1–3–6–9–12 months:DLQI (Dermatology Life Quality Index) (range 0–30) [30, 31].Patient-reported disease control at 1–3–6–9–12 months:RECAP (recap of atopic eczema) (range 0–28) [32].Patient-reported satisfaction with received treatment:PsoSat (Psoriasis care Satisfaction questionnaire) (range 0–30) [33].Cost-effectiveness at 3 and 12 months:EQ-5D-5L (EuroQol 5D 5L) (range 11,111–55,555) [34].Adapted iMCQ (iMTA Medical Consumption Questionnaire) [35].Adapted iPCQ (iMTA Productivity Cost Questionnaire) [35].Percentage of patients who achieve Treatment Target goals for AE at 3 (EASI50, delta PGA ≥  − 1), 6–9–12 months (EASI ≤ 7.0, PGA ≤ 2) [36].Adverse events of special interest (AEoSIs) and serious adverse events (SAEs) at 1–3–6–9–12 monthsPercentage of therapy failures and dropouts and reasons at 1–3–6–9–12 months, categorized according to Medical Dictionary for Regulatory Activities (MedDRA).

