#### Participant timeline

After screening and informed consent, participants will be randomized in the NB-UVB + OTT or OTT group. Study participation will entail 6 study visits. The baseline visit will take place before therapy starts. The follow-up visits are at 4 weeks, 3, 6, 9, and 12 months. Visits may be rescheduled within 1 month of the initial planning. Extra visit(s) will take place in case of therapy switch or stop. Patients in the NB-UVB + OTT group will undergo phototherapy 3 times a week for a planned period of 12 weeks from baseline, with a possible range of 8 to 16 weeks, depending on therapy response. Therapy duration will be determined in accordance to standard clinical practice. NB-UVB can be applied in the outpatient clinic or at home. Participants in both groups will apply daily OTT for a minimum of 3 months. Patients will be asked to keep all tubes of used OTT (excluding emollients) and bring them to the study visits. During the visits, data about NB-UVB and OTT will be collected. Patients will be asked for possible SAEs and AEoSIs with details such as start and stop date, intensity/severity of adverse events, probability of relation with NB-UVB + OTT or OTT, whether the allocated therapy was interrupted, and co-medications. During all visits, a physical examination by a blinded outcome assessor will take place to assess disease severity. Additionally, a set of questionnaires will be sent to the patient. The questions can be filled out on an electronic device, either at home or during the study visit in the outpatient clinic. At baseline, 3 months, and 12 months, an additional set of questionnaires regarding disease burden on productivity and medical costs will be filled out (Fig. 1). Subjects that have completed trial participation or have discontinued prematurely will be referred back to standard eczema care.

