### Statistical methods

#### Statistical methods for primary and secondary outcomes

The primary outcome measure will be estimated as a relative risk and absolute risk difference with 95% confidence interval and *p*-value. The primary outcome will be analyzed using a generalized linear model with binomial distribution and log-, or identity-link respectively. The primary analysis will be run using the intention-to-treat population. Missing data for the primary outcome is expected to be low, although meaningful drop-out can be expected.

A secondary analysis will be done using the per-protocol population. Exploratory subgroup analyses will be run, e.g., location of receiving NB-UVB (out-patient clinic or at home) and below or above the median EASI score at baseline.

Dichotomous secondary outcomes will be presented as counts, percentages, and relative risks according 95% confidence interval, and *p*-values will be calculated using the chi-square test or Fisher exact test as appropriate. Continuous variables will be presented as means with standard deviation when data distribution is normal. In case of skewed data medians with interquartile ranges will be used for presentation. The mean or median differences between the groups will be calculated with accompanying 95% confidence intervals using Satterthwaite’s or Hodges-Lehmann’s tests. Longitudinal data (repeated measures of, e.g., EASI, POEM, NRS-11, and EQ-5D-5L) will be analyzed using generalized estimating equations and adjusted for baseline values. Time to switching to systemic therapy will be analyzed as a time-to-event outcome using a Kaplan–Meier plot and log-rank test.

Multiple imputation will be used as necessary for secondary analyses and sensitivity analyses. The effects of intercurrent events will be assessed in sensitivity analyses. A detailed statistical analysis plan will be completed before the database lock.

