##### Adverse events of special interest (AEoSI)

An adverse event of special interest is defined as an undesirable experience occurring to a subject during the study, whether or not considered related to the study activities, that is of interest to this study. All AEoSIs reported spontaneously by the subject or observed by the investigator or his staff will be recorded and analyzed (Table 1).

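### Rescue medication, a secondary outcome, includes corticosteroid for NB-UVB sunburn, which only the NB-UVB arm can receive; 'use' compared on that definition would mix side-effect treatment with eczema rescue

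*Protocol article*

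**What the plan says.** The Rescue medication section of the protocol article puts three things under one term.

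- NB-UVB + OTT group only: "if sunburn occurs during NB-UVB, rescue medication consists of a one-time topical application of a class IV corticosteroid".
- All patients: "in case of severe uncontrolled AE during the study that requires rescue medication, a short course of oral prednisone can be prescribed".
- At the investigators' discretion: "rescue medication is allowed in other situations after consulting with the coordinating investigator".

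The Secondary outcome section lists use, amount and duration of rescue medication under the heading "Physician-reported clinical signs at 1–3–6–9–12 months". It does not restrict the outcome by drug or by indication.

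The OTT section bars the control group from an NB-UVB course during follow-up, so that group cannot meet the sunburn indication.

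On analysis, the statistical methods section states: "Dichotomous secondary outcomes will be presented as counts, percentages, and relative risks according 95% confidence interval", with p-values. It also states: "A detailed statistical analysis plan will be completed before the database lock".

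Sunburn is listed in Table 1 as an adverse event of special interest (AEoSI). For these events the article says: "All AEoSIs reported spontaneously by the subject or observed by the investigator or his staff will be recorded and analyzed". The Participant timeline section lists, among the details collected for each such event, "whether the allocated therapy was interrupted, and co-medications".

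**The concern.** One component of the definition treats a side effect of the tested intervention and is zero by design in the control arm. The outcome takes over the whole term. The most natural summary of 'use' is the proportion of patients with any rescue. On that summary a patient given one steroid application for a burn counts the same as a patient given prednisone for a severe flare.

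Two misreadings could follow. NB-UVB could appear to increase the need for rescue when eczema rescue is equal in the two arms. Or a real reduction in prednisone rescue could be diluted until it no longer shows. The effect on the NB-UVB proportion has only one possible direction, against NB-UVB. That matters in a superiority trial intended to inform whether this treatment keeps its place and its reimbursement.

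**Working it through.** **Inputs from the article.** Sample size section: 134 per arm for analysis, 15% drop-out, 316 in total, two-sided pooled Z-test at 5%. The recruited total reproduces: 2 × 134 = 268, and 268 / 0.85 = 315.3, rounded up to 316, or 158 per arm. These figures serve here only as arm sizes and as a test for illustration.

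**Inputs assumed.** The article gives neither of the following rates, and nothing in it favours one value over another.
- r: proportion with rescue for eczema, taken as 5% to 20%.
- s: proportion of the NB-UVB arm with corticosteroid for sunburn, taken as 1% to 10%.

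**Effect on 'any use'.** If the two kinds of rescue are independent, the NB-UVB proportion is 1 − (1 − r)(1 − s), a rise of s(1 − r) over r. Without independence, the proportion with either kind lies between max(r, s) and r + s, so the rise lies between max(0, s − r) and s. It is never negative.

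**Relative risk with equal eczema rescue, r = 10% in both arms** (true value 1.00, independence):
- s = 2%: 1 − 0.90 × 0.98 = 11.8%; 11.8 / 10 = 1.18
- s = 5%: 1 − 0.90 × 0.95 = 14.5%; 14.5 / 10 = 1.45
- s = 10%: 1 − 0.90 × 0.90 = 19.0%; 19.0 / 10 = 1.90

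**Chance of a falsely significant excess with NB-UVB.** This is an exact enumeration of two binomials with the pooled Z-test, counting only significant results in that direction. Without sunburn rescue it is about 2.5%.

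| s | 158 per arm: r = 5 / 10 / 15 / 20% | 134 per arm: r = 5 / 10 / 15 / 20% |
|---|---|---|
| 1% | 5.3 / 4.5 / 3.9 / 3.7% | 5.1 / 4.3 / 3.8 / 3.7% |
| 2% | 10.1 / 7.4 / 6.0 / 5.3% | 9.3 / 6.8 / 5.7 / 5.1% |
| 5% | 36.1 / 23.0 / 16.6 / 13.4% | 31.8 / 19.9 / 15.0 / 12.2% |
| 10% | 83.4 / 62.7 / 48.1 / 38.6% | 77.0 / 55.7 / 42.6 / 33.8% |

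**Chance of showing a true benefit.** Eczema rescue is taken as 10% with NB-UVB against 20% with OTT, a true relative risk of 0.50.

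| s | Observed relative risk | 158 per arm | 134 per arm |
|---|---|---|---|
| 0 | 0.50 | 70.8% | 63.7% |
| 1% | 10.9 / 20 = 0.545 | 61.2% | 54.4% |
| 2% | 11.8 / 20 = 0.59 | 51.3% | 45.2% |
| 5% | 14.5 / 20 = 0.725 | 24.9% | 22.1% |
| 10% | 19.0 / 20 = 0.95 | 4.0% | 4.0% |

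**Dependence on independence** (158 per arm, s = 5%). With r = 10% in both arms, the false-excess chance is 2.5% if every sunburn rescue falls in a patient who also has eczema rescue, 23.0% under independence, and 26.9% if the two never overlap. For the 10% v 20% benefit, the chance of showing it is 70.8% under full overlap and 21.1% under none.

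**The case against.** The strongest reply is that the harm needs an analysis the article does not state. It lists use, amount and duration together. A single topical application and an oral course share no unit of amount or duration, so a sensible report would separate them by type. Nothing names rescue as one of the dichotomous outcomes, and the detailed analysis plan is still to come. This stands in part. A reader might infer that a pooled yes/no comparison is planned, and the article does not support that. It also means that amount and duration are essentially unaffected. But the content of the outcome is set in the article itself, by a stated definition that differs between arms. An analysis plan that follows those words inherits the mixture.

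A second reply is that all rescue is a legitimate measure in a pragmatic trial of an add-on strategy, since treating its side effects is part of its burden. That is correct, but it answers a different question from eczema control and needs its own label.

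Third, a reader might infer from the clinical-signs heading that the outcome is declared a measure of disease control. The heading is too loose for that: it also holds topical therapy used and time to systemic therapy, which are not signs either. The case rests on the definition and does not need the heading.

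Finally, both rates are assumed, and if every sunburn rescue fell in a patient who also had eczema rescue, with s no larger than r, there would be no effect. That stands as well.

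**Conclusion.** The point holds as a minor flaw in the definition of one secondary outcome. The term rescue medication includes a treatment that only one arm can receive, for an indication that is not eczema, and the outcome uses the term without restriction. If 'use' is compared on that basis, the direction is known and the size is not.

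Under the assumed rates, independence and 158 per arm, the false-excess risk is modest at s = 1–2% (about 4–10% against 2.5%). It would be wrong to conclude from this that the issue is negligible whenever sunburn rescue is rare: the chance of showing a true 10% v 20% benefit falls from 71% to 61% at s = 1% and to 51% at s = 2%. Equally, the large figures at s = 5–10% are not predictions, because the article gives no sunburn rate.

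A reader might also infer that the trial's main result is at risk. It is not: the primary outcome, EASI50 at 3 months, and its sample size do not depend on how rescue is counted. Nor can the mixing produce a false claim of benefit, since it works only against NB-UVB.

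**What to change.** Before database lock, define the between-arm secondary outcome as use, amount and duration of rescue medication given for atopic eczema. Classify rescue in other situations by its recorded indication, and count it only when that indication is eczema. Report corticosteroid given for NB-UVB sunburn separately, for the NB-UVB arm, with the AEoSI sunburn. If a total of all rescue is also wanted, label it as treatment burden.

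The cost is one sentence in the outcome definition, one indication field if the form lacks it, and one more descriptive line in the tables. The two named treatments already differ by drug and route, and co-medications are collected with adverse event details, so only the discretionary category may need the new field. No safety information is lost, no patients, visits or tests are added, and the rescue treatment itself stays as planned.
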